# Effects of adaptive servo-ventilation therapy on cardiac function and remodeling in patients with chronic heart failure (SAVIOR-C): study protocol for a randomized controlled trial

**DOI:** 10.1186/s13063-014-0530-z

**Published:** 2015-01-16

**Keywords:** Adaptive servo-ventilation, Chronic heart failure, Noninvasive positive pressure ventilation, Left ventricular remodeling, Left ventricular ejection fraction, Cardiac function, Prognosis, Quality of life, Nonpharmacotherapy, Sleep-disordered breathing

## Abstract

**Background:**

Adaptive servo-ventilation (ASV) therapy, which is a form of noninvasive positive pressure ventilation therapy and uses an innovative ventilator that has simple operability and provides good patient adherence, potentially has therapeutic benefits—suppression of the deterioration and progression of chronic heart failure (CHF) and a reduction in the number of repeated hospitalizations. Therefore, ASV therapy draws attention as a novel, noninvasive nonpharmacotherapy for patients with CHF owing to its hemodynamics-improving effect, and it is currently being accepted in real-world clinical settings in Japan. However, clinical evidence sufficient for treatment recommendation is lacking because a multicenter, randomized, controlled study of ASV therapy has never been conducted.

**Methods/Design:**

The present study is a confirmatory, prospective, multicenter, collaborative, open-label, blinded-endpoint, parallel-group, randomized, controlled study. At 40 medical institutions in Japan, 200 Japanese outpatients with mild to severe CHF (age: ≥ 20 years; New York Heart Association classification: greater than or equal to class II) will be randomly assigned to either of the following two study groups: the ASV group, in which 100 outpatients undergo guideline-directed medical therapy and ASV therapy for 24 weeks; and the control group, in which 100 outpatients undergo only guideline-directed medical therapy for 24 weeks. The objective of the present study is to confirm whether the ASV group is superior to the control group concerning the improvement of left ventricular contractility and remodeling, both assessed by two-dimensional echocardiography. Furthermore, the present study will also secondarily examine the effects of ASV therapy on the prognosis and quality of life of patients with CHF.

**Discussion:**

ASV therapy using the device has the potential to provide therapeutic benefits based on its simple operability and good patient adherence and possesses the potential to improve left ventricular contractility and remodeling. Therefore, the present study is expected to afford more solid scientific evidence regarding ASV therapy as a novel, noninvasive, nonpharmacological, in-home, long-term ventilation therapy for patients with mild to severe CHF.

**Trial registration:**

UMIN identifier: UMIN000006549, registered on 17 October, 2011.

**Electronic supplementary material:**

The online version of this article (doi:10.1186/s13063-014-0530-z) contains supplementary material, which is available to authorized users.

## Background

In recent years, pharmacotherapy for chronic heart failure (CHF) has made remarkable progress. Furthermore, nonpharmacotherapies (for example, cardiac resynchronization therapy using an implantable cardioverter-defibrillator and comprehensive cardiac rehabilitation) have shown a given level of efficacy. However, patients with severe CHF still have a poor life prognosis and are often and repeatedly admitted to the hospital in the chronic clinical course of the disease. In addition, there are many patients whose symptoms of pulmonary congestion (for example, dyspnea and orthopnea) as well as quality of life are not sufficiently improved by existing therapeutic modalities.

Noninvasive positive pressure ventilation (NPPV) therapy has been reported to improve not only dyspnea and respiratory distress caused by cardiogenic pulmonary edema but also cardiovascular hemodynamics [1]. Namely, NPPV therapy is beneficial for both the respiratory and hemodynamic functions of patients with heart failure. In Japan, NPPV therapy is recommended for patients with acute heart failure who do not respond to oxygen therapy as a therapy categorized to class I in treatment recommendation and to A in evidence level [2]. These facts lead us to conjecture that NPPV therapy is potentially effective for patients presenting with symptoms that are attributable to the insufficient long-term management of pulmonary congestion/edema (for example, dyspnea at rest, intense fatigability, orthopnea, and paroxysmal nocturnal dyspnea). Nevertheless, NPPV therapy has not become established as a therapeutic modality for CHF because conventional medical devices for NPPV therapy are difficult to use for a long period due to their problems (for example, cumbersome operability of the devices and poor patient adherence).

Adaptive servo-ventilation (ASV) therapy, which is a form of NPPV therapy and uses an innovative ventilator AutoSet CS™ (Teijin Pharma Limited, Tokyo, Japan), potentially has the following mechanistic features that differ from conventional NPPV therapy including continuous positive airway pressure and bi-level positive airway pressure: 1) ASV therapy appropriately sustains ventilation by instantaneously detecting a decay in spontaneous ventilation of the patient and by providing support pressure in concert with his/her respiratory flow patterns; and 2) ASV therapy presents more physiological synchronization with the respiratory patterns [3]. ASV therapy potentially has therapeutic benefits—suppression of the deterioration and progression of CHF and a reduction in the number of repeated hospitalizations—based on the simple operability of the device and good patient adherence as compared with conventional NPPV therapy. Thus, it draws attention as a novel, noninvasive nonpharmacotherapy for patients with CHF owing to its hemodynamics-improving effect. Prior to the present study, we conducted a multicenter, retrospective, observational study [*S*tudy on the effects of *A*daptive servo-*V*entilation *I*n patients with chr*O*nic heart failu*R*e: *R*eal-world, multicenter, retrospective, observational study (SAVIOR-R)] for the objective of examining the real-world practical efficacy and limitations of ASV therapy for patients with CHF in Japan [4]. SAVIOR-R suggested that ASV therapy possibly improves the cardiac function and symptoms of patients with CHF, regardless of the severity of sleep-disordered breathing. Furthermore, prior single-center clinical studies indicated that ASV therapy improves left ventricular contractility and induces cardiac reverse remodeling [5], that pulmonary congestion improved by positive end-expiratory pressure suppresses sympathetic nerve activity [6-8], and that ASV therapy improves left ventricular ejection fraction (LVEF) and reduces brain natriuretic peptide levels [9] and further cardiac events (death and hospitalization) [10].

The present study is a confirmatory study of SAVIOR-R and aims to assess the effects of ASV therapy on left ventricular contractility and remodeling in patients with mild to severe CHF in a multicenter, randomized, controlled study. Left ventricular contractility and remodeling will be assessed by two-dimensional echocardiography.

## Methods/Design

### Study design and study organization

The present study (SAVIOR-C) is a confirmatory, prospective, multicenter, collaborative, open-label, blinded-endpoint, parallel-group, randomized, controlled study. The target number of patients is 200, and the study groups consist of the ASV group and the control group. The present study will last for 24 weeks, and the primary and secondary endpoints will be assessed at baseline (8 weeks prior to treatment onset through treatment onset), at week 12 of study (±4 weeks), on the day of study discontinuation, or on the day of study completion at week 24 (±4 weeks).

The Steering Committee will perform activities (for example, selection of study sites, investigators, and others, preparation and revision of the protocol and other documents, interpretation of questions about the study plan, coordination with investigators, establishment of the handling criteria for patients and data, determination of the acceptance of patients and data, interpretation of the study results, and preparation of study conclusions; Additional file 1). The Central Adjudication Committee will confirm in a blind manner the absence of any problems in measurement conditions and results of two-dimensional echocardiographic parameters, including LVEF—the primary endpoint—and in the subinvestigator’s assessment on CHF deterioration—the secondary endpoint, and will check whether adverse events and ventilator failure have developed in a biased fashion to a given group. The Study Promotion Committee will afford study support to study sites. The present study has been approved by the Ethical Review Board at each participating medical institution (Additional file 2) before its conduct in accordance with the Declaration of Helsinki. Prior to enrollment, all patients will provide written informed consent to be involved in the present study. The present trial is registered (UMIN identifier: UMIN000006549, registered on 17 October, 2011).

### Patients

SAVIOR-C will assign 200 Japanese outpatients with CHF, who meet all of the inclusion criteria and do not fall under any of the exclusion criteria (Table 1), to either of the following two study groups at 40 medical institutions in Japan based on assignment adjustment factors [age: < 65 years/≥ 65 years: gender: male/female:, and New York Heart Association (NYHA) classification: class II/III]: the ASV group and the control group (Figure 1).

**Table 1 Tab1:** **Inclusion and exclusion criteria**

**Inclusion criteria**	**Exclusion criteria**
1. Men and women	1. Patients with any of the following symptoms:
2. Age ≥20 years at informed consent acquisition	- Acute sinusitis or otitis media
3. Patients with CHF who are undergoing guideline-directed medical therapy	- Symptoms predisposing vomiting in the mask
4. Patients with CHF capable of using the ASV device at home as outpatients after enrollment	- Incapable of swallowing airway secretions
	- Pneumothorax or mediastinal emphysema
5. Patients whose NYHA class at baseline* is greater than or equal to II	- Recent cranial injury or surgery
6. Patients whose LVEF at baseline* is <40%	- Chronic hypoventilation
	2. Patients at risk of developing any of the following symptoms due to the use of the ASV device
	- Hypotension or a significant reduction in intravascular volume
	- Intense nasal bleeding leading to the risk of pulmonary aspiration
	3. Patients incapable of giving voluntary consent
	4. Patients with a history of undergoing the treatment of CHF by ASV at home
	5. Patients who are enrolled in another clinical study or trial
	6. Patients diagnosed with or suspected of dementia
	7. Patients whom the attending physician has considered ineligible for this study

*Week 8 before enrollment through day of enrollment. ASV, adaptive servo-ventilation; CHF, chronic heart failure; LVEF, left ventricular ejection fraction; NYHA, New York Heart Association.

**Figure 1 Fig1:**
[figure not shown]
**Flow diagram of SAVIOR-C.** AHI, apnea-hypopnea index; ASV, adaptive servo-ventilation; GDMT, guideline-directed medical therapy; NYHA, New York Heart Association.

### Study treatment

Study treatment initiates within 8 weeks after provision of the verbal and written explanations by the investigator to each patient. Eligibility check, enrollment, and randomization of each patient are performed between the provision and the study onset. Patients in the ASV group undergo ASV therapy in addition to guideline-directed medical therapy [11] for the study period (study onset through week 24 of study), while patients in the control group undergo only guideline-directed medical therapy for the study period. Patients in the ASV therapy group, who are in bed, undergo the ASV therapy each night during the study period.

### Endpoints

Efficacy, safety, and other aspects of ASV therapy will be assessed. The primary endpoint for efficacy is LVEF, a variable for the evaluation of heart failure that is applicable to a randomized controlled study of prospective, open-label, blinded-endpoint design. Two-dimensional echocardiography will be conducted at each institution in accordance with the procedures specified for SAVIOR-C. LVEF, left ventricular end-systolic volume, and left ventricular end-diastolic volume will be calculated according to the biplane Simpson’s method [12]. Furthermore, the Central Adjudication Committee will determine in a blinded fashion the acceptability of the echocardiograms to be submitted by the investigators.

The secondary endpoints for efficacy are 1) clinical events (death, hospitalization, treatment changes, and long-lasting (≥12 weeks) deterioration of symptoms) [13] to be finally adjudicated by the Central Adjudication Committee in a blind fashion, 2) brain natriuretic peptide to be measured at each participating medical institution, and 3) clinical composite response to be categorized (worsened, unchanged, and improved) based on NYHA classification and clinical events.

The endpoints for safety are adverse events and ventilator failure. The endpoints for other aspects of ASV therapy are as follows: 1) those to be collected via the case report form - patient background, quality of life, activities of daily living, vital signs, physical findings, echocardiograms, chest radiographs, hematology results, sleep study results (for example, apnea-hypopnea index), and usage of the ventilator, all from the ASV and control groups; and 2) those to be collected via electronic means—echocardiograms and air flow in the sleep study from the ASV and control groups, and usage of the ventilator from the ASV group. The schedule of observations, examinations, and assessments is shown in Table 2.

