### Statistical methods and sample size

The subgroup analysis of patients with reduced LVEF (<40%) in SAVIOR-R revealed a 6.9% improvement (before ASV therapy: 26.5 ± 7.4%; after ASV therapy: 33.4 ± 13.0%). In SAVIOR-R, furthermore, a statistical analysis considering time-course changes in LVEF indicated that the LVEF-improving effect of ASV therapy tended to appear at week 12 of the study or later. LVEF remained unchanged when ASV therapy was not conducted and improved by 5% when ASV therapy was conducted for 24 weeks. The target number of patients in SAVIOR-C was calculated based on an assumed standard deviation of 7.4 in reference to the pre-ASV therapy value. Consequently, power exceeds 80% when a group includes not less than 90 patients. Since sufficient power is obtained when a group includes 100 patients in consideration of a presumed withdrawal rate of 10%, a total of 200 patients—100 patients per study group—were established.

The efficacy analysis set consists of the full analysis set and the per-protocol set to be defined below. The full analysis set consists of patients who initiated ASV therapy, from whom the following patients are excluded: 1) patients in the ASV group who never used the ventilator during the study period; and 2) patients from whom the efficacy data after study onset were not obtained at all during the study period. The per-protocol set consists of patients in the full analysis set, from whom the following patients are excluded: 1) patients who deviated from the inclusion criteria or fell under any of the exclusion criteria; 2) patients who fell under any of prohibited combination therapies; and 3) patients with poor compliance in ventilator use. Poor compliance is defined as an ASV therapy practice rate of < 80% (number of days from day of treatment onset through day of treatment discontinuation or day of study completion). The safety of the study groups will be analyzed statistically on an intention-to-treat basis.

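### Treatment changes count as clinical events although unblinded physicians decide on them, so two of the three secondary efficacy endpoints are open to bias that blinded adjudication can only partly remove

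*Protocol article*

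**What the plan says.** The Study design and study organization section describes a "confirmatory, prospective, multicenter, collaborative, open-label, blinded-endpoint, parallel-group, randomized, controlled study". Under Study treatment, "patients in the control group undergo only guideline-directed medical therapy for the study period", so no sham device keeps the arm from patients or site staff.

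The Endpoints section lists three secondary efficacy endpoints. The first is "clinical events (death, hospitalization, treatment changes, and long-lasting (≥12 weeks) deterioration of symptoms", with a literature source attached and "to be finally adjudicated by the Central Adjudication Committee in a blind fashion". The second is brain natriuretic peptide. The third is "clinical composite response to be categorized (worsened, unchanged, and improved) based on NYHA classification and clinical events".

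The Study design section adds that the Central Adjudication Committee reviews, blind, the subinvestigator's "assessment on CHF deterioration—the secondary endpoint". So the site judges first and the committee reviews that judgement. The only restriction on background treatment that the article mentions is a per-protocol exclusion of "patients who fell under any of prohibited combination therapies".

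**The concern.** Death happens to a patient; a treatment change is something a physician does. In an open-label trial the physician acts knowing who has a device and who does not. If that knowledge alters the readiness to change drugs, the arms differ in real, correctly documented treatment changes even when ASV has no effect on the course of the disease.

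The abstract names prognosis as something the trial will examine secondarily, and the clinical-event endpoint is the one that speaks to it. The clinical composite response is built partly from the same events and inherits the component. A favourable result on either could then reflect how patients were managed rather than how they fared. The Discussion reports that Japanese cardiologists are taking up ASV rapidly because they expect it to help. That makes such an influence plausible, but does not prove it.

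**Working it through.** **1. What blinded adjudication can and cannot do.** Set the blinded final adjudication (Endpoints) beside the open-label design and the subinvestigator's first assessment (Study design):

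- A change is reported that does not reflect worsening heart failure: the committee can reject it.
- A change is made for some worsening, but would not have been made in the other arm: the record shows a genuine, qualifying change, and the committee has no ground to reject it.
- A change is withheld because the patient has a device: nothing is reported, and the committee has nothing to review.

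The last two cases remain even if only escalations for worsening count.

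**2. Which endpoints are reached.** Clinical events directly; the clinical composite response through its event part. Brain natriuretic peptide and LVEF do not contain the component. That is two of three secondary efficacy endpoints, and not the primary.

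**3. Illustration of size.** The article states no rate, power or test for the clinical-event endpoint, so there is no figure of the plan to reproduce here. From the plan: 100 patients per arm, or 90 after its presumed 10% withdrawal (100 × 0.90 = 90).

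Assumed, none of it from the document:
- other clinical events, h = 15% in both arms (no true effect);
- treatment changes, t = 15% in the ASV arm, and 20% or 25% in the control arm, the gap arising only from known allocation;
- treatment changes independent of other events;
- an any-event comparison by a two-sided 5% test of two proportions;
- rates that remain after adjudication.

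Any-event rate: p = 1 − (1 − h)(1 − t).

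- ASV: 1 − 0.85 × 0.85 = 0.2775
- Control, t = 20%: 1 − 0.85 × 0.80 = 0.3200 (difference 0.0425)
- Control, t = 25%: 1 − 0.85 × 0.75 = 0.3625 (difference 0.0850)

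Probability that the test favours ASV: Φ[(d − 1.96 × SE0)/SE1], where d is the difference, SE0 uses the pooled proportion and SE1 the two separate proportions.

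For t = 25%, n = 100:
- pooled p = 0.32; SE0 = √(2 × 0.32 × 0.68/100) = 0.0660
- SE1 = √((0.3625 × 0.6375 + 0.2775 × 0.7225)/100) = 0.0657
- (0.0850 − 0.1293)/0.0657 = −0.67, so Φ ≈ 0.25

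For t = 20%, n = 100:
- pooled p = 0.29875; SE0 = 0.0647; SE1 = 0.0647
- (0.0425 − 0.1269)/0.0647 = −1.30, so Φ ≈ 0.10

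A simulation of 400,000 trials gave 25.3% and 9.8%. With no gap the figure is 2.5%.

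**4. Sensitivity.** Probability of a significant result in either direction (5.0% with no gap), ASV rate of treatment changes 15%, other events at 10% to 20%:

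| Control rate of treatment changes | 90 per arm | 100 per arm |
|---|---|---|
| 20% | 8.7% to 10.6% | 9.2% to 11.2% |
| 25% | 20% to 27% | 21.7% to 29.3% |
| 30% | 38% to 51% | 41.6% to 54.8% |

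**The case against.** The strongest reply is that the committee does more than confirm that a change occurred. It reviews an assessment of heart failure deterioration and adjudicates events blind, so it can discard changes not prompted by worsening. That stands, and it limits the problem, but it does not reach changes made or withheld because the arm was known.

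A second reply is that this belongs to every open-label, blinded-endpoint trial, and that hospitalization is exposed too. Also true: any remedy that keeps hospitalization reduces the bias without removing it. Components still differ in how much discretion they carry, and the article itself defends LVEF as suited to this design.

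A reader might go further and infer that treatment changes are counted without regard to direction: that a drug reduction after improvement is an event, that starting or stopping ASV is one, or that any change makes a patient with improved NYHA class count as worsened. The article does not support this. It frames the secondary endpoint as deterioration, cites a source for the event list, and does not state how NYHA class and events are combined. Definitions may sit in the full protocol or an adjudication charter, and an article commonly omits them. Nor does anything show that treatment changes are the most frequent component.

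Finally, the illustration assumes the gap it then measures. That is correct: it shows susceptibility only.

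**Conclusion.** The point holds in a limited form. Including treatment changes leaves the clinical-event endpoint and the clinical composite response open to a difference driven by known allocation, which blinded adjudication reduces but cannot remove. The article shows that such a bias is possible, not that it exists or which way it runs.

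The figures of about 10% and 25% rest wholly on the assumed rates, on independence of the components and on an any-event analysis that the article does not specify. They should not be read as an estimate for this trial. Because the primary endpoint and the confirmatory echocardiographic objective are outside this point, it is an inexpensive improvement rather than a threat to the main conclusion.

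**What to change.** In the Endpoints section:

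1. State that any conclusion on prognosis rests on blindly adjudicated death or hospitalization.
2. Report treatment changes and long-lasting symptom deterioration as separate, supportive components.
3. Report the clinical-event endpoint and the clinical composite response also without the treatment-change component.

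No rule on patient treatment changes. Table 2 already schedules background therapy, NYHA class and cardiac events at both post-baseline visits, so little or no new data should be needed. The article says the trial is ongoing and that the analysis plan will be prepared before database lock, which leaves room to specify these analyses.

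The cost is fewer qualifying events and less precision on a secondary endpoint. Some exposure remains: physicians who know the arm can also influence hospitalization, and NYHA class in the composite response is recorded at open-label sites.
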